## Methods

### Design

This is a multi-centre two-arm pilot RCT exploring the feasibility and potential effectiveness of CBT for relatives of missing persons suffering from psychopathology, in comparison with a waiting list control group. The intervention group will start with the treatment within 1 week after randomisation. The waiting list control group will receive the treatment 12 weeks after randomisation. An allocation ratio of 1:1 will be used. The participants will be asked to fill in questionnaires prior to the treatment and 1, 12, and 24 weeks post-treatment. Participants in the waiting list control group will complete an additional questionnaire 1 week prior to their actual start of the treatment. In addition, the participant will be asked to complete a brief questionnaire at the start of each session to assess the potential change in repetitive negative thinking, intrusive memories, and self-compassion during the treatment.

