### Sample size

To find a within-subjects difference in PCBD symptom across four time points (baseline and 1, 12, and 24 weeks post-treatment) of medium effect size [19] with a power of 80 %, an *α* of 0.05, assuming the correlation between the measures to be 0.50, a sample size of in total 24 participants is sufficient. By taking into account a drop-out rate of 19 %, based on a review that reported a mean attrition rate of 19 % among studies that evaluated the effectiveness of CBT for bereavement-related psychopathology [19], a total sample size of 29 is required.

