#### Other measures

Sociodemographic variables (e.g., gender, date of birth, and educational level) of the participants and missing persons will be registered at the first measurement occasion. The number of sessions the participants attended will be registered at the 1-week post-treatment assessment. In case the participant attended less than eight sessions, the reason(s) for drop-out will be registered. The following two open-ended questions regarding the evaluation of the treatment will also be administered at the 1-week post-treatment assessment: “About which aspects of the treatment are you satisfied?” and “About which aspects of the treatment are you less satisfied?”. The questionnaires and time points are summarised in Table 1.

**Table 1 Tab1:** Overview of variables, concepts, measures, and time points

Variable	Concept	Measure	Time points
Primary outcome measures	Severity of PCBD symptoms	ICG	T0, T0.1, T1, FU1, FU2
Secondary outcome measures	Severity of PTSD symptoms	PCL-5	T0, T0.1, T1, FU1, FU2
	Severity of depressive symptoms	IDS-SR	T0, T0.1, T1, FU1, FU2
	Extent of mindfulness	SMQ	T0, T0.1, T1, FU1, FU2
Mediator	Severity of grief cognitions	GCQ	T0, T0.1, T1, FU1, FU2
	Severity of rumination	RRS	T0, T0.1, T1, FU1, FU2
	Severity of repetitive negative thinking	PTQ	T0, T0.1, T1, FU1, FU2
	Ability to be self-compassionate	SCS	T0, T0.1, T1, FU1, FU2
	Severity of intrusive memories	TMQ	T0, T0.1, T1, FU1, FU2
	Severity of avoidance behaviour	DAAPGQ	T0, T0.1, T1, FU1, FU2
Process of change session by session	Ability to be self-compassionate	SCS-SF	Start of each treatment session
	Severity of intrusive memories and images	Intrusive memories and images vas	Start of each treatment session
	Frequency of repetitive negative thinking	RNT vas	Start of each treatment session
Other variables	Sociodemographic information		T0
	Evaluation of the treatment and reason(s) for drop-out		T1

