*ICG* Inventory of Complicated Grief, *PCL-5* Posttraumatic Stress Disorder Checklist for DSM-5, *IDS-SR* Inventory of Depressive Symptomatology—Self-Report, *SMQ* Southampton Mindfulness Questionnaire, *GCQ* Grief Cognition Questionnaire, *RRS* Ruminative Response Scale, *PTQ* Perseverative Thinking Questionnaire, *SCS* Self-Compassion Scale, *TMQ* Trauma Memory Questionnaire, *DAAPGQ* Depressive and Anxious Avoidance in Prolonged Grief Questionnaire, *SCS-SF* Self-Compassion Scale – Short Form, *RNT vas* Repetitive Negative Thinking visual analogue scale, *T0* baseline measure, *T1* post-treatment assessment, *T0.1* post-waiting period measure, *FU1* follow-up measure 1, *FU2* follow-up measure 2

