##### Data analyses

Within-subjects repeated measures ANOVA with time (baseline, 1, 12, and 24 weeks post-treatment) as the repeated measure will be performed to evaluate the effects of the treatment in terms of changes in mean scores of PCBD.

Between-subjects multivariate analysis of covariance (MANCOVA) will be performed to compare changes in PCBD, MDD, PTSDD, and mindfulness scores between the treatment and waiting list condition. Specifically, scores at post-treatment (in the treatment condition) and post-waiting period (in the waiting list condition) on measures tapping these phenomena will be compared, including baseline scores as covariates.

Within-subjects MANCOVA with time (baseline, 1, 12, and 24 weeks post-treatment) as the repeated measure will be performed to evaluate the short- and long-term effects of the treatment in terms of change in mean scores of PCBD, MDD, PTSD, and mindfulness. To test whether the treatment effect is mediated by changes in cognitive variables (i.e., grief cognitions, intrusive memories, rumination, and repetitive negative thinking), behavioural variables (i.e., avoidance behaviour), and self-compassion, only the scores of measures tapping these constructs that show the strongest association (based on univariate analyses) will be added to a multiple regression model. Finally, to assess the potential change at micro-level in repetitive negative thinking, intrusive memories and self-compassion throughout the course of the treatment a within-subjects repeated measures ANOVA with time (session 1 to session 8) as the repeated measure will be performed with mean scores of measures tapping repetitive negative thinking, intrusive memories, and self-compassion as outcome measures.

Data will be analysed according to the intention-to-treat principle. Missing data will be handled using multiple imputations. The Statistical Package for the Social Sciences will be used for the analysis. The small sample size of the pilot RCT increases the risk of type II error; the preliminary results regarding the potential effectiveness will therefore be reported with caution following the recommendations for conducting a pilot study [78].

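### The within-subjects analyses start from T0 in both arms, so change during the waiting list's untreated weeks enters the pooled pre-post change

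*Protocol article*

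**What the plan says.** Under Data analyses, the primary analysis is described as follows: "Within-subjects repeated measures ANOVA with time (baseline, 1, 12, and 24 weeks post-treatment) as the repeated measure will be performed". It has one factor, time, and no group term. The within-subjects MANCOVA on all four outcomes uses the same four time points.

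The Table 1 legend fixes the labels: "T0* baseline measure, *T1* post-treatment assessment, *T0.1* post-waiting period measure". The row for the primary outcome reads "Severity of PCBD symptoms ICG T0, T0.1, T1, FU1, FU2", so the Inventory of Complicated Grief is taken both before and after the wait.

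The Design section gives the timing. For the CBT arm: "The intervention group will start with the treatment within 1 week after randomisation". For the other arm: "The waiting list control group will receive the treatment 12 weeks after randomisation". It adds: "Participants in the waiting list control group will complete an additional questionnaire 1 week prior to their actual start of the treatment".

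The between-group MANCOVA also uses the word baseline, there for its covariate: "scores at post-treatment (in the treatment condition) and post-waiting period (in the waiting list condition) on measures tapping these phenomena will be compared, including baseline". For a waiting-list participant whose outcome is the post-waiting score, that covariate can only be T0.

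On numbers, the Sample size section concludes that "a sample size of in total 24 participants is sufficient" for the four-time-point analysis. The abstract plans 15 participants per arm.

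**The concern.** The ANOVA is meant to evaluate the effects of the treatment. In the CBT arm T0 comes shortly before therapy, so T0 to T1 is a pre-post interval. In the waiting-list arm T0 comes before the wait, so T0 to T1 is the wait plus the therapy. The score that stands directly before therapy in that arm, T0.1, is not a level of either within-subjects analysis.

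If both arms are pooled with T0 as the first level, whatever happens during the wait is credited to treatment in the waiting-list part of the sample, and the first level means different things in the two arms. The primary estimate, which is to inform a larger trial, would then mix treated and untreated change.

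**Working it through.** **1. Are both arms in the primary analysis?** Inputs from Sample size: four time points (m = 4), correlation ρ = 0.50, α = 0.05, power 80%, medium effect. The article gives no number for medium; Cohen's f = 0.25 is assumed. For a within-factor F test under sphericity, λ = f²·N·m/(1 − ρ), with df₁ = m − 1 and df₂ = (N − 1)(m − 1).

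| N | λ = 0.0625 × N × 4 / 0.5 | Power |
|---|---|---|
| 12 | 6.0 | 0.467 |
| 15 | 7.5 | 0.578 |
| 23 | 11.5 | 0.797 |
| 24 | 12.0 | 0.817 |

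The plan's 24 is reproduced. A single arm of 15 would have power 0.58, so the calculation makes sense only if treated waiting-list participants are included.

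**2. Which score is baseline?** Three places agree. The legend equates baseline with T0 and gives T0.1 a different name. The between-group MANCOVA uses baseline in a sense that can only be T0. The Design section calls the extra waiting-list questionnaire additional to the common series. The list of four time points is the same in Study objectives, Sample size and Data analyses, and T0.1 is in none of them.

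**3. How long is the interval?** Treatment lasts at most 12 weeks (Treatment section) and T1 follows 1 week later. Counted from randomisation to T1:

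- CBT arm: at most 1 + 12 + 1 = 14 weeks
- Waiting-list arm: at most 12 + 12 + 1 = 25 weeks

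The difference is 25 − 14 = 11 weeks. T0.1 itself falls 12 − 1 = 11 weeks after randomisation. The untreated part is therefore about 11 weeks up to T0.1, or 12 up to the start of therapy.

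**4. Size of the bias.** Let w be the fall in score, in SD units, during the wait, and let half the analysed sample be waiting list. The pooled change is shifted by ½·w + ½·0 = w/2. The documents give no w; 0.2 to 0.4 SD is an assumed range, so the shift is 0.10 to 0.20 SD.

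For scale, with means in the pattern (0, d, d, d), f = d·√3/4. Then f = 0.25 corresponds to d = 0.25 × 4/√3 = 0.577 SD. The shift is 0.10/0.577 = 17% to 0.20/0.577 = 35% of that step.

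**5. Effect on the F test with an inert treatment.** At N = 24, λ = (3d²/16) × 24 × 4/0.5 = 36d², with d = w/2:

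| w (assumed) | Shift d | λ | P(significant time effect) |
|---|---|---|---|
| 0.2 | 0.10 | 0.36 | 7.1% |
| 0.3 | 0.15 | 0.81 | 9.9% |
| 0.4 | 0.20 | 1.44 | 14.2% |

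A simulation (20,000 runs, 12 of 24 participants shifted) gave 7.2% at w = 0.2 and 9.7% at w = 0.3. With T0.1 as the waiting-list baseline it stayed at about 5% for every w tried. These figures assume that natural change stops when therapy starts.

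**6. If natural change does not stop.** Suppose instead that scores drift by w per 12 weeks, so that both arms also drift by about w from the start of treatment to T1, and keep the step pattern. With T0.1 as the waiting-list baseline the shift is w, and the rates are 14.2% (d = 0.2) to 47.6% (d = 0.4). With T0 throughout the shift is 1.5w, and they are 28.0% (d = 0.3) to 84.8% (d = 0.6).

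**The case against.** Four points can be made in the plan's favour.

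- **No sentence says that waiting-list participants enter the ANOVA with T0.** The Design section also speaks of questionnaires before treatment, and T0.1 is one of those; an unseen analysis plan could settle the matter. It stands that pooling and the waiting-list baseline are inferred from definitions and the sample size. A reader might infer that the article openly prescribes the wrong score; it does not. What it does is define baseline as T0, use it so elsewhere, and offer no substitution.
- **The direction is unknown.** A reader might infer that the bias favours the treatment. The Background argues that grief after a disappearance is longer lasting, and no figure for untreated change is given. Change during the wait could be near zero, or a worsening that hides a benefit.
- **Much of the false-positive risk is not specific to this point.** A reader might take 5% against 7% to 14% as the whole story, or suppose that the correction restores a 5% error rate. Step 6 shows that neither holds if drift continues. Participants in both arms are selected on the same elevated scores, so regression to the mean also sits in the CBT arm's change, and moving the waiting-list baseline leaves it there.
- **The setting limits the damage.** This is a pilot, results are to be reported with caution, and the randomised comparison adjusted for T0 does control for change during the wait. That comparison is secondary, however, so it mitigates the problem in the primary estimate without removing it.

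In addition, relatives of the same missing person share an arm, so the waiting-list share of completers need not be exactly one half; the bias is that share times w.

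**Conclusion.** The point holds as a flaw in how the pre-treatment level is defined. Followed literally, the primary ANOVA and the within-subjects MANCOVA count about 11 to 12 untreated weeks as treatment for roughly half the sample, and bias the pooled change by about w/2 SD in whichever direction scores move. The conclusion rests on pooling, which the required total of 24 implies, and on the legend's definition of baseline. The numerical size rests on an assumed w and on an equal split of completers; the error rates in step 5 also need natural change to stop at the start of therapy.

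Severity: should be fixed. The estimate is affected, but nothing is lost in the data and the randomised comparison is sound on this point.

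**What to change.** Add one sentence to Data analyses: in every within-subjects analysis of treatment change, the pre-treatment level is T0 for the CBT arm and T0.1 for the waiting-list arm. Report the waiting-list change from T0 to T0.1 separately, as the untreated change. Keep T0 as the covariate in the between-group MANCOVA.

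The cost is negligible. T0.1 is already collected on every outcome and mediator, the ANOVA still has four levels, and 24 completers still give power 0.817 under the same assumptions.

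The text should also say what this does not cure: natural change during treatment and follow-up, and regression to the mean in the CBT arm, remain uncontrolled in any pre-post analysis.

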**Methods:**

A pilot RCT comparing participants of the CBT condition (*n* = 15) with waiting list controls (*n* = 15) will be executed. Individuals suffering from psychopathology related to the long-term disappearance of a loved one are eligible to participate. The treatment consists of eight individual sessions. Questionnaires tapping psychological constructs will be administered before, during, and after the treatment. The feasibility of the treatment will be evaluated using descriptive statistics (e.g., attrition rate). The primary analysis consists of a within-group analysis of changes in mean scores of persistent complex bereavement disorder from baseline to immediately post-treatment and follow-up (12 and 24 weeks post-treatment).

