### Study objectives

The aim of this pilot study is to evaluate the feasibility and the potential effectiveness of CBT with elements of mindfulness in reducing PCBD, MDD, and PTSD symptoms and enhancing the extent of mindfulness among relatives of missing persons. Based on previous studies, we expect that the treatment effect will be mediated by changes in negative cognitive and behavioural variables plus enhancement of self-compassion.

The feasibility of the pilot RCT will be explored by the evaluation of the (1) specifics of potential participation bias, (2) attrition rate, (3) methods used and study design, (4) treatment fidelity, and (5) strengths and suggestions for improvements of the treatment from the perspective of the participant. The primary objective of the analysis of the pilot RCT is to assess changes in mean scores on a measure of PCBD from baseline to 1, 12, and 24 weeks post-treatment. A within-group instead of a between-groups analysis will be executed because this will give the most rigorous information about the potential effects of this treatment given the small sample size.

Secondary objectives of the analysis of the pilot RCT are (1) to evaluate whether the mean scores on measures tapping PCBD, MDD, PTSD, and mindfulness of the treatment group differ from the waiting list control group at the post-treatment/post-waiting period assessment when adjusting for the baseline scores and (2) to test whether the treatment effect is mediated by changes in negative cognitive variables (i.e., reductions in negative grief cognitions, intrusive memories, rumination, and repetitive negative thinking) and behavioural variables (i.e., avoidance behaviours) and enhancement of self-compassion. In addition, the extent of change in repetitive negative thinking, intrusive memories, and self-compassion in response to the treatment will be explored at micro-level by means of tracking measures tapping these constructs during the treatment.

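### The mediation analysis keeps only the mediators with the strongest univariate association and tests them on the same 24 to 30 people, which inflates false positives; as described, the regression does not by itself test mediation

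*Protocol article*

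**What the plan says.** Study objectives sets as a secondary objective "to test whether the treatment effect is mediated by changes in negative cognitive variables", together with avoidance behaviour and self-compassion. Table 1 lists six scales as mediators: GCQ, RRS, PTQ, SCS, TMQ and DAAPGQ. All are measured at the same occasions as the outcomes (T0, T0.1, T1, FU1, FU2).

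The method is one sentence under Data analyses: of the candidate measures, only those that "show the strongest association (based on univariate analyses) will be added to a multiple regression model". The sentence does not say what the association is with, how strong it must be or how many measures may be kept. It mentions no allowance for the selection.

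The rest of that section does not compare the mediators between arms. The between-arm MANCOVA and the within-subjects MANCOVA both cover PCBD, MDD, PTSD and mindfulness, none of which is a candidate mediator. The session-by-session ANOVA covers related constructs, but within treated participants and with different instruments.

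The Abstract plans 15 participants per arm. Sample size states that "a sample size of in total 24 participants is sufficient" for the primary within-group analysis. No size is given for the mediation analysis.

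**The concern.** There are two problems, and they differ in how firmly the text supports them.

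- **Selection.** Choosing the strongest of six candidates and then testing it on the same data is a stated rule. The winner's p-value ignores that it won, and its coefficient is too large on average.
- **Target.** Mediation needs the treatment to move the mediator and the mediator to carry effect to the outcome. A coefficient of outcome on mediator addresses only the second part. Two self-report scales can move together whether or not treatment moved either.

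The Discussion lists evaluation of possible mechanisms of change as a strength and expects the pilot to inform a large-scale RCT. A mediator chosen by this rule could therefore carry more weight in planning that trial than the evidence supports.

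**Working it through.** **Inputs.** From the article: six candidate scales (Table 1), 30 participants planned (Abstract), 24 sufficient for the primary analysis (Sample size), and "an *α* of 0.05". Assumed, because the article gives no values: the correlation among the six scales (0 to 0.7) and the true mediator-outcome correlation (0.2 to 0.6).

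**The plan's own figure.** The article gives an effect "of medium effect size" (taken here as Cohen f = 0.25, an assumption), "assuming the correlation between the measures to be 0.50", and m = 4 time points. For a one-group repeated-measures ANOVA, λ = n·m·f²/(1 − ρ). At n = 24, λ = 24 × 4 × 0.0625 / 0.5 = 12 with 3 and 69 degrees of freedom, and power is 0.817. At n = 23 it is 0.797. So 24 reproduces, but it concerns the primary analysis only.

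**Step 1: independence bound.** The chance that at least one of six independent null tests at 5% is significant is 1 − 0.95⁶ = 0.265.

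**Step 2: simulated selection under the null.** Six candidates unrelated to outcome; take the largest |r| and test it at a two-sided 5%. The critical |r| is t/√(n − 2 + t²): 2.074/√(22 + 2.074²) = 0.404 at n = 24, and 2.048/√(28 + 2.048²) = 0.361 at n = 30.

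| Intercorrelation | Strongest significant, n = 24 | n = 30 | Mean \|r\| of strongest, n = 24 | n = 30 |
|---|---|---|---|---|
| 0 | 26% | 26% | 0.34 | 0.31 |
| 0.3 | 24% | 24% | 0.33 | 0.30 |
| 0.5 | 21% | 21% | 0.32 | 0.28 |
| 0.7 | 17% | 17% | 0.29 | 0.26 |

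One mediator fixed in advance would give 5% and a mean |r| of 0.17 (n = 24) or 0.15 (n = 30). The table assumes that one winner is tested.

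**Step 3: does the rule find a real mediator?** With n = 30 and one candidate truly correlated with outcome, that candidate is the one picked in 39% to 53% of trials at r = 0.3 and in 64% to 87% at r = 0.5 (intercorrelation 0.7 down to 0).

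**Step 4: is the coefficient a test of mediation?** First take a single mediator-outcome pair with no selection and no treatment effect. The correlation is significant in 15% (n = 24) to about 18% (n = 30) of trials at r = 0.2, in 30% to 37% at 0.3, and in 73% to 83% at 0.5.

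Then add selection and put arm in the model. Assumptions: six candidates intercorrelated 0.5, a direct treatment effect of 0.5 SD, treatment moves no mediator (so true mediation is zero), and one candidate has coefficient b on outcome.

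| b | Selected coefficient significant, n = 24 | n = 30 |
|---|---|---|
| 0 | 20% | 20% |
| 0.3 | 44% | 49% |
| 0.5 | 78% | 86% |
| 0.6 | 90% | 96% |

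At b = 0.5 and n = 30, also requiring a significant arm-to-mediator difference cuts 86% to about 4%. In a run with real mediation (treatment shifts all six scales by 0.8 SD, b = 0.5, direct effect 0.3 SD), the coefficient alone is again significant in 86% of trials. It does not separate mediation from its absence.

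**The case against.** The article gives mediation one sentence in a condensed description. That sentence opens by stating the mediation aim, so an arm term and path estimates are compatible with it, and a fuller plan not shown could supply them. This stands. A reader might infer that the plan never estimates a mediated effect, but the document shows only that none is described. The second problem is therefore conditional on the coefficient alone being read as mediation. The selection rule is different: it is stated, and adding an indirect effect would not remove it.

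A reader might also infer that the plan will very probably find a mechanism even if treatment does nothing. The documents do not support that. The 73% to 83% in Step 4 is the ordinary power of one pair at an assumed correlation of 0.5 and involves no selection. At 0.2 it is 15% to 18%. The article gives no mediator-outcome correlation; its 0.50 is between repeated measures of the outcome. Nor does the rule simply select noise: the Background gives theoretical grounds for the candidates, and Step 3 shows that a strong true mediator is usually picked.

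Finally, this is a secondary objective of a pilot, and the Discussion asks for cautious interpretation and verification in later studies. That limits the consequence. However, the specific caution under Data analyses concerns type II error, and the problem here is false positives.

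**Conclusion.** The concern holds in two parts. Without qualification, selecting the strongest of six mediators and testing it on the same 24 to 30 people raises the nominal 5% to about 17% to 26% under no association. It also gives the winner a mean |r| of about 0.26 to 0.34. These figures rest on an assumed intercorrelation of 0.7 to 0 and on one winner being tested. Conditionally, if the regression coefficients alone are read as mediation, they do not test it, because no described analysis compares the six scales between arms. How often such a coefficient would mislead depends on an unknown mediator-outcome correlation, so only a range can be given. The point is worth correcting before the data are analysed. It does not touch the primary within-group result or the feasibility results.

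**What to change.** Delete the univariate selection. On the randomised data (T0 to T1 in the treatment arm, T0 to T0.1 in the waiting list arm), estimate for all six scales, or for one or two named in advance:

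1. the effect of arm on the post-period mediator, adjusted for the baseline mediator;
2. the effect of the post-period mediator on the post-period ICG, adjusted for arm, baseline ICG and baseline mediator.

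Report every indirect effect (the product of the two) with a bootstrap 95% confidence interval, and label them all exploratory. Relatives of the same missing person are allocated together, so resample by missing person where the number of clusters allows. State that mediator and outcome are measured at the same occasion, so their order in time cannot be shown.

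No new data are needed; the cost is a change of wording and a few models. The intervals will be wide and the mechanism claim weaker. Keeping all six scales leaves several estimates without formal multiplicity control, which is why all must be reported; naming one or two in advance reduces this but gives up breadth.
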